## Abstract

**Background:**

Decreasing salt consumption can prevent cardiovascular diseases (CVD). Practically, it is difficult to promote people’s awareness of daily salt intake and to change their eating habits in terms of reducing salt intake for better cardiovascular health. Health education programs visualizing daily dietary salt content and intake may promote lifestyle changes in patients at high risk of cardiovascular diseases.

**Methods/Design:**

This is a cluster randomized trial. A total of 800 high-CVD-risk patients attending diabetes and hypertension clinics at health centers in Muang District, Chiang Rai province, Thailand, will be studied with informed consent. A health center recruiting 100 participants is a cluster, the unit of randomization. Eight clusters will be randomized into intervention and control arms and followed up for 1 year. Within the intervention clusters the following will be undertaken: (1) salt content in the daily diet will be measured and shown to study participants; (2) 24-hour salt intake will be estimated in overnight-collected urine and the results shown to the participants; (3) a dietician will assist small group health education classes in cooking meals with less salt. The primary outcome is blood pressure change at the 1-year follow-up. Secondary outcomes at the 1-year follow-up are estimated 24-hoursalt intake, incidence of CVD events and CVD death. The intention-to-treat analysis will be followed.

Blood pressure and estimated 24-hour salt intake will be compared between intervention and control groups at the cluster and individual level at the 1-year follow-up. Clinical CVD events and deaths will be analyzed by time-event analysis. Retinal blood vessel calibers of CVD-risk patients will be assessed cross-sectionally. Behavioral change to reduce salt intake and the influencing factors will be determined by structured equation model (SEM). Multilevel regression analyses will be applied. Finally, the cost effectiveness of the intervention will be analyzed.

**Discussion:**

This study is unique as it will recruit the individuals most vulnerable to CVD morbidity and mortality by applying the general Framingham CVD risk scoring system. Dietary salt reduction will be applied as a prioritized, community level intervention for the prevention of CVD in a developing country.

**Trial registration:**

ISRCTN39416277

## Background

Cardiovascular diseases (CVD) are the world’s largest killers, causing more than 17 million estimated deaths globally in 2008
[1]. Over 80% of these CVD deaths occurred in low- and middle-income countries
[1]. There is an urgent need to prevent CVD morbidity and mortality in developing countries
[2]. In Thailand, CVD events are currently in the top three leading causes of death
[3] and leading causes of admissions to provincial and community-level hospitals
[4]. Thus, prevention of CVD events in high-risk individuals would be the most cost-effective strategy for reducing the morbidity and mortality caused by CVD in low-middle-income countries such as Thailand
[5].

Salt reduction at the community level is the WHO-suggested strategy for prevention of CVD in developing countries
[2,6-8]. In recent years, it has become a proven, effective strategy in many countries such as Finland, Japan and some developed countries
[6,9-11]. In Asia, strokes are common CVD events, with hypertension as the most attributable risk factor for CVD; consequently, salt intake is likely to be the most important risk behavior to be controlled for CVD prevention
[12]. However, evidence for implementation of reducing salt intake in the developing country setting is still scarce and inadequate, especially in Southeast Asian countries
[13]. The cost effectiveness of the salt reduction strategy for CVD prevention is also yet to be determined
[14].

Human beings love the taste of salt, and the consumption of salty foods has become a well-entrenched dietary habit
[15]. Many patients with CVD risks know that a high level of salt intake is a risky behavior. However, changing the behavior to a reduction in salt intake is not easily done in practice. It is necessary to strengthen the hearsay knowledge and relayed massage among the high-risk persons so that a strong perception will develop, leading to behavioral change
[16]. “Seeing is believing”
[17]. We hypothesized that visualizing the salt content in daily food and the rough amount of individual daily salt intake in high-risk persons could lead to behavioral change.

In this study, we will research intensive health education interventions that use visualization tools to make individuals aware of their daily salt consumption. The participants will be informed of the salt content in a variety of daily foods as well as their 24-hour estimated salt intake by urine sodium measurement. The health promotion strategy aims to reduce salt intake to prevent CVD. The implementation of the strategy will be centered at community health centers in Chiang Rai province in northern Thailand. It is expected to bring about behavioral changes leading to voluntary salt reduction among high-risk patients, thereby averting thousands of CVD events and deaths.

## Methods/Design

### Study objectives

The primary objective is to compare the effectiveness of health education via visualization of salt content in food, soup and urine, with routine health education by means of measuring blood pressure changes in high-CVD-risk patients at 1-year follow-up.

The secondary objectives are: to compare the effectiveness of specially designed health education with routine health education by means of monitoring estimated daily salt intake using urine sodium measurement, CVD incidence and retinal vessel caliber changes among diabetic and hypertension patients with high CVD risk. We will also compare the cost-effectiveness of health education via visualization of salt content in food, soup and urine with routine health education among diabetic and hypertensive patients with high CVD risk.

### Design

This is a cluster randomized controlled trial (CRT). The rationale for choosing a CRT design is to prevent contamination by sharing second-hand massage between participants of intervention and control arms. Instead of randomizing the individual patient, clusters of eligible patients will be randomly allocated into the intervention and control arms. There will be two arms of CRT: the salt reduction intervention arm and control arm. The units of randomization are health centers.

### Study site: clusters and characteristics of the clusters

The study will be conducted in Muang district, Chiang Rai, the northernmost province of Thailand. Every health center within the study site district, which has a hypertension and diabetes clinic, will be screened for eligibility criteria. In order to prevent an empty cluster, any health center with a total of fewer than 200 patients attending the hypertension and diabetes clinic will not be included. In this study, one health center will form one cluster. Each cluster will have 100 participants, and there will be four clusters in each study arm. The locations of randomly allocated clusters are as shown in Figure
1. The study has been carefully designed to minimize the coefficient of variation among the clusters.

**Figure 1 F1:**
[figure not shown]
Map showing study area and clusters.

### Map of the study area

#### Study population

In this study, the study population will comprise high-CVD-risk patients stratified by the Framingham general CVD risk scoring system
[18,19]. Only those patients who have a CVD risk score higher than 15% will be included.

### Eligibility criteria for individual patients to enroll in the study

Selection of participants will be according to the following inclusion and exclusion criteria.

#### Inclusion criteria

1. Diabetic patients with high CVD risk according to the Framingham general CVD risk score (>15%)

2. Hypertensive patients with high CVD risk according to the Framingham general CVD risk score (>15%)

3. Patients who are willing to participate in the study

#### Exclusion criteria

1. Any female patients who are pregnant or trying to become pregnant

2. Patients aged younger than 35 years

3. Patients with documented type I diabetes

4. Those on long-term steroid therapy (more than 2 weeks)

5. Those on long-term non-steroidal anti-inflammatory drugs (NSAIDs) (i.e., every day for at least 1 year)

6. Patients with cancer

7. Patients with known secondary hypertension such as primary aldosteronism, Cushing’s syndrome or pheochromocytoma

8. Patients with severe chronic pulmonary diseases using home oxygen therapy

9. Patients with chronic renal disease (creatinine ≧ 2.0 mg/dl)

10. Patients with congestive heart failure

11. Those with known previous diagnosis of CVD

### Ethical approval

The study protocol was approved by the Juntendo University Ethics Committee, Japan (no. 2011036) on 1 July 2011 and Chiang Rai Regional Hospital Ethics Committee, Thailand (no. CR0027.102/research/207) on 17 November 2011. The study has been registered as a current controlled trial internationally, and International Standard Randomized Controlled Trial Number Register ISRCTN39416277 was assigned on 3 January 2012
[20].

Participants will be well informed about the study process in their respective group of the study and will be free to decide to participate in the trial (Autonomy)
[21]. There are no racial or ethnic criteria for inclusion in the study (Equity). Participants in both the control and intervention groups will receive routine health services and also some trial-related screening service benefits such as salt intake estimation, lipid profile, hemoglobin A1c and body composition measurements (Table
1). There will be no introduction of risk to the participants (Beneficence).

**Table 1 T1:** Overview of data collection and measurements in both CRT arms

	**Follow-up**												
Visit number	1	2	3	4	5	6	7	8	9	10	11	12	13
Month	0	1	2	3	4	5	6	7	8	9	10	11	12
Inclusion and exclusion criteria	x												
Framingham score	x			x									x
Estimated 24-hour salt intake, overnight urine	x			x									x
Blood pressure	x	x	x	x	x	x	x	x	x	x	x	x	x
Body composition	x			x									x
Blood glucose	x												
HbA1c	x												
Lipid profile	x												
BUN, creatinine	x												
Sodium, potassium	x												
Uric acid	x												
CVD event	x			x									x
CVD death	x			x									x
Retinal caliber	x												
Demographic characteristics	x												
Questionnaires assessing behavioral change	x			x									x
Questionnaires assessing health costs	x			x									x

### Enrollment

There are 31 health centers in Muang District. We will apply the criterion that there must be a minimum of 200 patients attending the diabetes and hypertension clinics in the health centers. (Figure
2)This selection criterion is set in order to obtain a sufficient number of high-CVD-risk patients with a high enough Framingham general CVD risk score (>15%) within the study site clusters. Using the existing provincial databases for screening, eight health centers meet this criterion.

**Figure 2 F2:**
[figure not shown]
** Flow chart for enrollment and follow-up plan for CRT.**^*****^The eligibility criteria refer to the inclusion and exclusion criteria under the heading of study population. ^+^Clusters are shown in Figure
1.

#### Randomization and application of eligibility criteria

A statistician, blinded to the recoded number of health centers, will generate the random allocation sequence using Stata software, version 11 (College Station, TX, USA). Simple randomization will be used to allocate the eight clusters into intervention and control groups. (Figure
2)

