### Sample size

For a conventional randomized control trial, a total of 240 participants, randomizing 120 into each arm, will have enough power (90%) to detect the minimal difference of systolic blood pressure 130 (±20) and 120 (±20) mmHg, diastolic pressure 90 (±20) and 80 (±20) mmHg, difference in 24-hour estimated salt intake 10 (±5) and 8 (±4) g/day and CVD event rate of 0.15% and 0.08% between the control and intervention group with a 95% confidence interval
[6,31]. The cluster randomized trial design used in RESIP-CVD might result in loss of power and reduced efficiency. In this cluster randomized trial, the number of participants in each cluster will be the same, and other variable factors such as geography, food tradition, race and dietary habits are assumed not to be different for delineating the intracluster coefficient. To compensate the design effect, the inflation factor has been calculated by the formula (*Deff* = 1 + (*m–1*)*ρ*) where *Deff* is inflation factor for design effect, *m* is the size of each cluster, which is 30 and *ρ* is the intracluster coefficient which is assumed to be 0.07. The sample required for a cluster randomized trial was inflated to 720. With a loss to follow-up of approximately 10%, we expect that the sample size of 800 patients will yield sufficient power to detect the desired minimal difference in primary and secondary outcomes between the intervention and control group. All eight clusters of the RESIP-CVD study will enroll 100 eligible participants.

We identified the confounders and planned to collect the information for multivariate analysis adjustment. (Table
4)

**Table 4 T4:** Confounder measurements

**Confounder**	**Variables**	**How to measure**
Demographic characteristics	Age, sex, social status, family size, educational attainment, occupational history, income	Questionnaire
Lifestyle	Smoking, alcohol	Questionnaire
Genetic factor	Family history of diabetes/hypertension	Questionnaire
Drugs	Different medications for diabetes and hypertension	Clinical record

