[38]. The cost-effectiveness analysis of our study is expected to answer these questions for developing countries.

We have designed the study to have minimal residual confounding factors and selected practical and contemporary approaches that overcome hard-to-achieve lifestyle modifications. Thus, we expect that implementing a health promotion intervention trial in a practical setting will yield comprehensive and applicable evidence for global reduction of CVD deaths and prevention of CVD events.

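### The stated simple randomisation of eight health centers does not secure the planned four per arm, and no allocation step or stated 1-year test deals with chance imbalance in blood pressure between arms

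*Protocol article*

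**What the plan says.** The Design section of the protocol article makes the health center the unit of allocation: "The units of randomization are health centers". The Enrollment section gives the number available: "Using the existing provincial databases for screening, eight health centers meet this criterion". Under the heading on randomization and application of eligibility criteria, a statistician generates the sequence in Stata, and "Simple randomization will be used to allocate the eight clusters into intervention and control groups". No fixed-number draw, blocking, stratification, matching or constraint is described.

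The study site section fixes the result: "Each cluster will have 100 participants, and there will be four clusters in each study arm".

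Three statements bear on comparability of clusters:
- Study site section: "The study has been carefully designed to minimize the coefficient of variation among the clusters".
- Sample size section: "other variable factors such as geography, food tradition, race and dietary habits are assumed not to be different". The same section uses an intracluster coefficient of 0.07.
- Discussion: "We have designed the study to have minimal residual confounding factors".

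The Analysis plan compares mean blood pressure between arms at 1 year by Student's *t* test or a non-parametric test, at individual and cluster level. Table 1 schedules blood pressure at month 0. Table 4, the list of confounders for adjustment, does not contain baseline blood pressure or any cluster-level variable.

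**The concern.** Simple randomisation normally means that each unit is allocated independently with probability one half. With eight units the split is then itself random, and an equal one is not the most likely result. A plan that names this method and also states a fixed 4:4 split leaves the reader unable to tell how the allocation was made.

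The second issue is balance. With only eight units, sizeable differences between arms in starting blood pressure can easily arise by chance. The protocol says that cluster variation was minimised and residual confounding kept small, but it gives no allocation step that would do this. If the arms start several mmHg apart, an unadjusted comparison at 1 year is hard to interpret and less precise than it need be.

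**Working it through.** **Inputs.** From the protocol article: 8 clusters (Enrollment); 4 per arm and 100 per cluster (study site section); SBP 130 against 120 mmHg with SD 20, 95% confidence, ICC 0.07, *m* = 30 in the design effect and 10% loss (Sample size). The 10% loss leaves 90 analysed per cluster.

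**The plan's own figure.** 240 × [1 + (30 − 1) × 0.07] = 240 × 3.03 = 727, against 720 stated; 720 / 0.9 = 800. So the total of 800 is reproduced to within rounding. The article gives no probability for the 4:4 split.

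**Split under simple randomisation.** The number of clusters in the intervention arm is Binomial(8, 0.5), and there are 2^8 = 256 equally likely sequences.
- 4:4: C(8,4)/256 = 70/256 = 27.3%
- 5:3: 2 × 56/256 = 43.8%
- 6:2: 2 × 28/256 = 21.9%
- 7:1: 2 × 8/256 = 6.3%
- 8:0: 2/256 = 0.8%

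Hence 6:2 or worse: (56 + 16 + 2)/256 = 74/256 = 28.9%.

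**Power for SBP by split.** The variance of a cluster mean is 20² × [1 + 89 × 0.07]/90 = 400 × 7.23/90 = 32.13. For *a* and *b* clusters per arm, SE = √[32.13 × (1/*a* + 1/*b*)]. Power is from a two-sided 5% *t* test on 6 df for a 10 mmHg difference.

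| Split | SE (mmHg) | Variance relative to 4:4 | Power |
|---|---|---|---|
| 4:4 | 4.01 | 1.00 | 55% |
| 5:3 | 4.14 | 1.07 | 53% |
| 6:2 | 4.63 | 1.33 | 44% |
| 7:1 | 6.06 | 2.29 | 29% |

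An 8:0 split allows no comparison. With the normal approximation in place of *t* on 6 df, the powers are 70%, 68%, 58% and 38%.

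**Balance under a fixed 4-of-8 draw.** I assume that the SD of 20 and the ICC of 0.07 also describe baseline SBP; the article does not say so.
- Between-cluster SD: √(0.07 × 400) = √28 = 5.3 mmHg.
- Variance of a baseline cluster mean with 100 participants: 400 × [1 + 99 × 0.07]/100 = 400 × 7.93/100 = 31.7.
- SD of the difference between arms: √[31.7 × (1/4 + 1/4)] = √15.9 = 4.0 mmHg.
- Chance of a baseline difference of 5 mmHg or more in either direction, which is half the target effect: 2 × [1 − Φ(5/3.98)] = about 21%.

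As an illustration for a yes/no cluster trait held by 4 of the 8 centers: among the 70 possible draws it splits 2:2 in 36 (51.4%), 3:1 in 32 (45.7%) and 4:0 in 2 (2.9%).

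**The case against.** **The statements may be compatible.** A reader might infer that the randomization and study site sections cannot both be true. That goes too far. They agree by chance in 27% of literal draws, and always if simple is used loosely for an unstratified draw of 4 from 8. The study site section refers to a map of randomly allocated clusters, participants are recruited at centers that have already been allocated, and Trial status says recruiting. The draw has therefore probably been made and may well have given 4:4. Nothing in the article shows an unequal allocation. This objection stands and reduces the first issue to a description that must be reconciled.

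**Power.** A reader might blame simple randomisation for the gap between the planned 90% power and 55%. That gap is present at 4:4 and comes from the cluster size used in the design effect and the few degrees of freedom, which is a separate matter. The most likely unequal split, 5:3, costs only about 2 points. Only 6:2 or worse matters. Nor does the Sample size section fix four per arm; it says only that all eight clusters enrol 100. The split is fixed in the study site section.

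**Control of cluster differences.** The plan does limit heterogeneity: one district, at least 200 clinic patients per center, 100 participants each and a Framingham risk above 15%. Randomisation also balances in expectation, and a correct cluster-level analysis carries chance imbalance in its standard error. So it would be wrong to say that the design gives no balance or is biased. The list of factors assumed not to differ is also narrower than it may seem: it does not include clinic size or blood pressure control. But these features restrict who enters; they do not balance the arms, and an ICC of 0.07 itself concedes that clusters differ.

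**Analysis.** The abstract names blood pressure change as the primary outcome and mentions multilevel regression, and Table 4 plans adjustment for individual-level confounders. An analysis of change would take account of baseline in part. But the Analysis plan specifies a comparison of 1-year means, and neither it nor Table 4 includes baseline blood pressure.

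**Conclusion.** The point holds in two parts.

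1. The named method, read as written, produces the stated 4:4 split in 27% of draws, and 6:2 or worse in 29%, where SBP power falls from 55% to 44% or lower. The two sections must be reconciled. The documents do not show that the actual allocation was unequal.

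2. Whatever simple was meant to convey, no allocation step assures balance between two arms of four centers. The chance difference in baseline SBP has an SD of about 4 mmHg against a 10 mmHg target, with about a 21% chance of 5 mmHg or more, and the stated 1-year *t* test does not adjust for it. This is a loss of precision and interpretability, not proof of bias.

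The figures rest on the protocol's SD of 20 and ICC of 0.07, on applying both to baseline SBP, on 90 analysed per cluster for power and on 100 per cluster for baseline.

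**What to change.** **If allocation is not yet done:** replace simple randomisation with a random draw of 4 of the 8 centers. Preferably constrain it: list the 70 possible 4:4 allocations, keep those acceptably balanced on clinic size and, where the provincial database holds them, on mean SBP or diabetes share, then draw one at random. The article confirms only that the databases were used to screen for the 200-patient criterion, so the other variables need checking. If a randomisation test at p < 0.05 is wanted, keep more than 40 allocations: the smallest two-sided p is 2/*N*, and 2/40 is exactly 0.05. If allocations are kept in mirror pairs, keep at least 42 (2/42 = 0.048).

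**If allocation is done:** state how 4:4 was obtained and correct the word simple. Constrained allocation is then no longer available.

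**In either case:** adjust the primary 1-year blood pressure comparison for baseline blood pressure, as an individual covariate or as the cluster mean, in an analysis that respects clustering. Used as a cluster-level covariate, the baseline mean takes one of the 6 degrees of freedom.

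The cost is small. Month-0 blood pressure is already collected, so the change is one corrected sentence and a little analysis work, plus a short task for the statistician if the draw is still to come.

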#### Concealment of allocation

The study objectives will be clearly explained to the directors of the health centers, the cluster representatives. Informed consent and agreement to enroll in the study will be requested before random allocation into either arm of the study. Up until the point of enrollment, the researcher and cluster representative cannot know the allocation of the clusters. Only after the agreement to enroll, the enrollment and the random allocation will the procedures, applicable to their particular study group, be explained to the cluster representatives, and this will be done on different days.

At the allocated health center, participants will be recruited by fulfilling the eligibility criteria for individual enrollment. Written informed consent for trial participation will be requested of eligible participants. Likewise, the study participants will not know into which arm of the study they will be allocated until they have enrolled in the study. The participants will receive a thorough explanation of the procedures of the arm to which their attending health center has been randomly allocated. They will not be informed or will be unaware of the fact that there is another group in the study, nor will they be informed of the procedures of the other arm.

Each health center will enroll 100 participants. Chronology of the recruitment is as follows: When the patients come to the health center for their routine check-up, they will be invited to participate in the trial. On the next visit, the eligibility criteria will be checked, and informed consent will be obtained from those who are eligible. Then, the participants will receive a detailed explanation of the procedures of their respective study arm.

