#### Blinding

The cluster representatives will know their allocated arm after random allocation, and the study procedure of only their allocated arm will be explained to them. Individual participants will be given information pertaining to the study group in their allocated cluster only after enrollment, and thus blinded. The nature of the study does not allow double blinding. However, the cluster randomized trial design will prevent contamination between the two arms of the study.

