### Baseline survey

In this CRT, we wanted to test the health intervention in high-CVD-risk patients. A low incidence of CVD events in low-CVD-risk patients may warrant a larger sample size than that we calculated and a longer follow-up than we can perform. Therefore, we will recruit only the high-CVD-risk patients stratified by using the Framingham general CVD risk scoring system (10-year risk). Calculation of the Framingham score will require information such as age, sex, smoking status, systolic blood pressure, history of taking antihypertensive drugs, history of diabetes and body mass index (BMI).

After recruitment, the Framingham score of the eligible patients will be assessed in a baseline survey
[19,20]. The risk score calculator in formula excel spread sheet published by the Framingham Heart Study will be distributed to the study site HCs
[32]. HC staffs will be trained to apply it for the CVD risk stratification.

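### Centres are randomised and their directors told the arm before patients are invited, scored and consented, so the concealment described does not prevent differential recruitment between arms

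*Protocol article*

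**What the plan says.** The section Concealment of allocation deals first with the centres. Of the directors it says: "Informed consent and agreement to enroll in the study will be requested before random allocation into either arm of the study". It adds: "Up until the point of enrollment, the researcher and cluster representative cannot know the allocation of the clusters". The Blinding section dates the directors' knowledge: "The cluster representatives will know their allocated arm after random allocation, and the study procedure of only their allocated arm will be explained to them".

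The same section then turns to patients: "At the allocated health center, participants will be recruited by fulfilling the eligibility criteria for individual enrollment". It sets out two steps. First: "When the patients come to the health center for their routine check-up, they will be invited to participate in the trial". Then: "On the next visit, the eligibility criteria will be checked, and informed consent will be obtained from those who are eligible". The procedures of that centre's arm are explained to the patient directly afterwards. Patients are not to learn their arm until they have enrolled, and they are not told that another group exists.

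Eligibility needs a Framingham general CVD risk score above 15%. The Baseline survey section says of the score calculator: "HC staffs will be trained to apply it for the CVD risk stratification". On its inputs it says: "Calculation of the Framingham score will require information such as age, sex, smoking status, systolic blood pressure, history of taking antihypertensive drugs". Each centre enrols 100 patients, and the Enrollment section requires at least 200 patients in a centre's diabetes and hypertension clinics.

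**The concern.** In a cluster randomised trial, concealing the allocation from the centre's director protects the decision of the centre to join. It does not protect the later decision about which patients to enrol. If that second decision is taken by people who know the arm, the two arms can recruit different kinds of patient even though the centres were allocated fairly.

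The risk matters here because the intervention works through awareness and behaviour change. Staff at an education centre could, without any ill intent, invite patients whom they think likely to engage, while control centres invite whoever attends. The arms would then differ at baseline in motivation, salt habits or blood pressure. Such a difference does not shrink as more patients are enrolled, and covariates remove it only so far as they measure it. The confounders listed in Table 4 are demographic characteristics, smoking and alcohol, family history and medication. Motivation is not among them, nor are baseline blood pressure and baseline salt intake.

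**Working it through.** The point rests on the order of steps, not on a stated figure, so the check is to put the steps in sequence and ask at each one who knows the arm.

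1. The director agrees to enrol the centre. Nobody knows the arm (Concealment of allocation).
2. The eight centres are allocated by simple randomisation (Randomization and application of eligibility criteria).
3. The director learns the arm and that arm's procedures (Blinding).
4. Patients at the centre, which is now allocated, are invited at a routine check-up. The director knows the arm; the patient does not.
5. At the next visit eligibility is checked and consent taken. Knowledge is as in step 4. Health-centre staff are the people trained to use the risk calculator.
6. The arm's procedures are explained to the enrolled patient. From the first patient to reach this step, anyone at the centre who gives or hears the explanation can tell the arm, while the rest of the 100 are still to be recruited.

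Two readings need settling.

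*What enrolment means in the concealment sentence.* The statement that the researcher and the cluster representative cannot know the allocation until enrolment could be taken to mean enrolment of patients. The paragraph around it concerns directors and centres, and the Blinding section dates the directors' knowledge from randomisation. Two other places agree with that order: the section on the study site already refers to a map of the allocated clusters, and Trial status says that participants are being recruited. The sentence therefore covers steps 1 and 2, not steps 4 and 5.

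*Who does the recruiting.* Invitation, eligibility check and consent are written without naming who performs them. Only directors are said to know the arm. That the recruiting staff know it follows from where they work and from step 6. It is a strong inference, but not a statement in the text.

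Against steps 4 and 5, the article describes these restraints:

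- The patient's unawareness of the arm limits self-selection by patients.
- The cut-off of >15%, computed in a spreadsheet mainly from fixed items such as age, sex and diabetes history, limits discretion in scoring.
- Neither acts on the choice of which attenders to invite.

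**The case against.** The strongest reply has four parts.

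*The source is a condensed article.* The enrolment flow chart is not visible, and the full protocol may say how the 100 are chosen, for instance consecutively. This stands: the absence of a selection rule here is not a finding. What can be criticised is the chronology that the article does set out, in which the arm is disclosed before patients are selected.

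*Staff knowledge is not stated.* This also stands, and the point is worded as an inference for that reason. A reader might infer that the document says the score is calculated by staff who know the arm. It says only that health-centre staff are trained to apply the calculator.

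*There are real safeguards.* Directors are told only their own arm's procedures, patients are unaware of the arm until enrolled, and eligibility has a numeric threshold. These narrow the opening but do not close it. Systolic blood pressure does enter the score, and blood pressure is the primary outcome. A reader might infer a known bias from that, but the same threshold applies in both arms and the document gives neither a direction nor a size.

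*The scope for selection is unknown.* A reader might infer from 100 enrolled out of 200 that half the patients can be passed over. The 200 is a minimum count of all clinic patients, before the risk threshold and the eleven exclusion criteria. A centre near that floor may have few eligible patients beyond 100, and a larger clinic may have many. The eligible pool is not given, so no fraction follows.

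**Conclusion.** The point holds as a weakness of the stated procedure: it protects the allocation of centres and keeps patients unaware of their arm until they enrol, but it does not prevent differential recruitment by people who know the arm. It rests on the order given in Concealment of allocation and Blinding, and on the inference that recruiting staff learn the arm no later than the first enrolled patient's explanation. The concealment of the centre-level allocation is adequate as described and is not questioned.

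The size of any bias cannot be derived. A reader might wish to set an assumed shift in systolic pressure against the 10 mmHg target difference or against a standard error. The document supports no value for the shift and states no standard error. A computed one depends heavily on the cluster size. With SD 20, 400 per arm and an intracluster coefficient of 0.07, m = 100 gives a design effect of 1 + 99 × 0.07 = 7.93 and a standard error of √(2 × 20² × 7.93 / 400) = 3.98 mmHg. The sample-size section's m = 30 gives 1 + 29 × 0.07 = 3.03 and √(2 × 20² × 3.03 / 400) = 2.46 mmHg. Neither says anything about how large a recruitment bias would be. Nor does the document show that biased recruitment has taken place.

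**What to change.** At each centre, complete identification of patients, eligibility scoring, consent and baseline measurement before the arm is disclosed to the centre, its director included.

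Clusters are already allocated and recruitment is under way, so some centres may know their arm. For those:

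- Have someone outside the centre fix the order of invitation, as a random or consecutive list from the clinic register. The provincial database could serve instead if it holds patient-level data; the article mentions it only for screening centres.
- Keep a log, by arm, of every patient invited, found ineligible, refusing and enrolled, and report it with the results so that readers can judge whether recruitment differed.

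The cost is later disclosure and a later start of the intervention at each centre. The delay is at least the two-visit recruitment period and longer if 100 patients take more time to accrue; baseline salt intake also needs three successive days of measurement. Timings that the plan counts from enrolment would have to be checked against the later disclosure. The log adds some record keeping. No additional patients are needed.
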